### Follow-up Surveys

Monthly surveys will be carried out at monthly intervals after baseline and finishing in December in both years. The questionnaire will collect data on compliance, acceptability of the lotion and malaria exposure that month. An RDT will also be carried out to actively detect malaria cases. Positive results will be confirmed by PCR in London where possible and a random selection of negative RDTs will also be confirmed in this way. Positive cases are to be given prompt treatment according to local guidelines.

The access to many villages is anticipated to become very difficult during the height of the rainy season and the study aims to continue data collection by using village health volunteers (VHVs). These volunteers have already been trained in the use of RDTs and malaria treatment and will be further trained to give out replacement repellent/placebo and complete the monthly survey forms.

Access to remote communities is anticipated to be a major obstacle in data collection, particularly during the rainy season. The use of VHVs will hopefully enable data collection to continue throughout these months. The monthly survey has been designed to be as simple as possible to enable these workers who sometimes have limited education to complete the form.

### Exit Survey

An exit survey will be carried out during the final month of data collection, which will assess the acceptability of the repellent lotion in more detail. Another blood spot will be collected from each participant.

## SAFETY CONSIDERATIONS

### DEET Safety

DEET was first registered for use as an insect repellent over 50 years ago; it is effective against a wide range of insects and still remains the most widely used repellent today, with an estimated 200 million annual applications (Barnard 2000). However, DEET has been linked to adverse events following high exposures, primarily involving seizures and encephalopathy in children (Osimitz and Grothaus 1995). Qiu *et al.* (1998) reviewed the safety of DEET and found the compound associated with cases of encephalopathy, seizures and dermatitis; however concluded that DEET was safe when used appropriately given that the incidence of adverse effects was very low when its widespread use was considered.

About 5-8% of applied DEET is absorbed into the skin, but is subsequently completely metabolised and mostly excreted in the urine within four hours (Selim *et al.* 1995). Veltri *et al.* (1994) reviewed over 9,000 calls to American Poison Control Centres involving DEET exposure. Over half of exposures had no symptoms at the time of the call, and symptoms usually occurred through inhalation or contact with eyes. Almost 90% of exposures were treated solely at home, and 80% of those referred to a health centre were discharged after initial examination, suggesting mild or short-lived symptoms. Severity of symptoms was more closely related to the type of exposure than the concentration of DEET, or the age or gender of the patient. The United States Environmental Protection Agency reviewed DEET safety and concluded that it was not possible to identify DEET as the cause of seizures or encephalopathy and that there was no unreasonable risk to human health when used according to product instructions (USEPA 1998).

The safety of DEET use in pregnant women was assessed during a clinical trial of the product for the prevention of malaria (McGready *et al.* 2001b). No adverse neurological, gastrointestinal or dermatological effects were reported and neither were there any adverse effects on survival or development of the babies at birth or one year. Antwi *et al.* (2008) carried out a risk assessment of DEET use by humans. Based on animal tests a no-observed-effect-level (NOEL) was set at 200 mg DEET per kg body weight for acute toxicity, and 500 mg DEET per kg body weight dose per day was set for chronic toxicity.

## DISCONTINUATION CRITERIA

### Participant and Household Withdrawal

Participants may withdraw their consent to take part, as well as permission for their children to take part at any point before the end of the trial. If withdrawal takes place in the first two months of the trial, then further recruitment within the same village will be considered.

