### Potential Risks and Benefits

Finger-prick blood spots do cause modest, brief discomfort but are common in use in this area and it is likely most individuals will have already experienced this. Risk from this procedure is very low and antiseptic wipes are used to prevent infection.

Use of repellent is universal worldwide and present extremely low risk. We are using a high quality commercial brand made, registered and sold in the USA by SC Johnson. We are using the lowest effective dose of active 15% DEET and a consumer friendly gentle aqueous lotion formulation to minimise risk and discomfort. As young children have a lower body volume / skin surface ratio we will not enrol anyone under six years old. Full USA compliant consumer product information will be given verbally and in local language on the products. Any contraindications or side effects will be recorded and reported for appropriate action to local District Health departments. All positive cases will be referred for immediate treatment following local guidelines through the District Health teams working with us on the study. Treatment for *P. falciparum* with co-artem is free at the point of delivery in Lao PDR.

If findings are positive there would be a strong case for the use of repellents as part of future vector-borne disease control programmes.

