### Randomisation

Randomisation to repellent or placebo lotion will take place at the household level and is stratified by village. All the households in a village will be assigned to either group 258 or 305 (manufacturer codes of repellent and placebo lotions) during the baseline survey. District health workers who recruited and carried out the baseline survey labelled straws with the group codes which the heads of households then picked.

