### Recruitment and Baseline Survey

Recruitment will take place in May 2009, when 300 households will be recruited from Attapeu province, and in April 2010, when 1,300 households will be recruited from both Attapeu and Sekong provinces. Participants will be recruited as volunteers from meetings with village members and local health team staff where the study will be described in full with opportunity for questions. Individuals that wish to take part will also receive this information in writing and sign a consent form to confirm they understand the trial, including the possibility they may receive the placebo lotion. A maximum of 25% of households will be recruited from any village in order to overcome diversion of bites to non-repellent users. In addition district health staff will be responsible for ensuring that study houses contain at least five eligible participants (if the household is bigger, more can be recruited), and that study houses are distributed throughout the village, the rule being that study houses should be a minimum of 10m apart. The baseline survey is scheduled for the same time as recruitment, May 2009 and April 2010. The questionnaire, estimated to take 30 minutes, will collect basic information on wealth indicators and current malaria prevention behaviour for the household and individual information on malaria exposure.

Households will be randomly assigned to one of the treatment groups and supplied with three 100ml bottles per person per month to allow for 10ml use per day as well as sufficient LLINs for the whole household, including non-participants (sufficient LLINs defined as one net for every 1.5 persons in the household, plus another for use away from home). District health staff will demonstrate how to use the lotion and explain that it should be used every evening. Participants will also be encouraged to use the lotion during the day if they notice biting.

A bloodspot will also be taken from each participant and stored on filter paper for laboratory analysis for dengue, JE and typhus. Analysis will ideally take place in Laos if facilities can be found, but if this is not possible the bloodspots will be transported to the UK or France for testing.

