## DATA HANDLING AND RECORD KEEPING

### Data Analyses and Handling

Only the consent forms will contain personal information (names) and these will be stored for the length of the trial in a locked filing cabinet in the project office in Vientiane. Number codes will be used to identify participants during baseline and monthly surveys. Data will be entered into a password protected Microsoft Access database.

The initial analysis will be performed according to intention-to-treat. This will include all participants who were recruited to the trial and gave every monthly RDT result. An additional per protocol analysis will be carried out. This will include only those participants who slept under a bed net and used the lotion in the evenings at least 90% of the time. Positive cases will be subsequently excluded from the trial due to the possibility of them testing positive in later months from the same episode.

Data from both arms from baseline surveys will be compared by ANOVA. Comparison of *P. falciparum*, *P. vivax* and fever incidence between the trial arms will be carried out by poisson regression adjusted for intracluster (household) variation by random effects methods. Comparison of seroconversion for dengue, Japanese Encephalitis and scrub typhus between trial arms will be done using a chi-squared test on numbers seroconverted or not seroconverted over the course of the trial.
An assessment of compliance will be carried out looking in particular at repellent and placebo use and LLIN use. Adverse events in children under 12 years and in participants over 12 years will also be assessed.

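### Early withdrawals may be met by new recruitment, but the protocol gives recruits no allocation and its intention-to-treat rule excludes most of them, along with early leavers

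*Protocol*

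**What the plan says.** Four parts of the protocol bear on this.

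- **Participant and Household Withdrawal.** Leaving is open throughout: "Participants may withdraw their consent to take part, as well as permission for their children to take part at any point." The next sentence is the replacement rule: "If withdrawal takes place in the first two months of the trial, then further recruitment within the same village will be considered." It does not say whether the recruit is a person or a household, how the recruit gets an arm, or whether outcomes are still collected from the person who left.
- **Randomisation.** The unit and the stratum are stated: "Randomisation to repellent or placebo lotion will take place at the household level and is stratified by village." On timing, the section says that each village's households "will be assigned to either group 258 or 305 (manufacturer codes of repellent and placebo lotions) during the baseline survey", by heads of household drawing coded straws.
- **Recruitment and Baseline Survey.** "Households will be randomly assigned to one of the treatment groups" as part of recruitment, which is scheduled together with the baseline survey. No later draw is described.
- **Data Analyses and Handling.** The initial analysis is called intention-to-treat, and its membership is defined: "This will include all participants who were recruited to the trial and gave every monthly RDT result."

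**The concern.** The replacement rule and the analysis rule do not fit together. One invites people in after follow-up has begun. The other admits only people who were tested at every round. Either the recruits contribute nothing to the main analysis, or the membership rule has to be reinterpreted after the fact.

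The same membership rule removes early leavers once their testing ends, so the set is defined by something that happens after randomisation. Leaving could differ by arm. The Blinding section accepts that the lotions may be told apart by a slight smell, and the DEET Safety section lists dermatitis among reported associations. If it does differ, the people compared are no longer the groups the straws created.

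Allocation is a further gap. If a person is added to a household already in the trial, the lotion is in use there when that person decides to join. This is recruitment after allocation in a household-randomised trial, and blinding staff to the codes does not remove the risk.

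**Working it through.** **1. The plan's own figures.** The only nearby figure is the 27% by which the Sample Size Calculation raises 633 households per arm: 633 × 1.27 = 803.9, which reproduces the stated 804. Table 4 attributes this increase to non-compliance. The protocol gives no withdrawal rate, by arm or by reason, so the point rests on reading the sections together.

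**2. How many results a recruit can give.** The Study Schedule lists follow-up in July to November 2009 (5 rounds) and May to November 2010 (7 rounds), with exit in December. The Follow-up Surveys section runs monthly testing to December, so I count December as a round: 5 + 1 = 6 and 7 + 1 = 8.

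- Joined after round 1: at most 6 − 1 = 5 of 6, or 8 − 1 = 7 of 8.
- Joined at the end of month 2: at most 6 − 2 = 4 of 6, or 8 − 2 = 6 of 8.

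Neither meets the requirement of a result at every round. Only a recruit who joins before round 1 could. Later recruits qualify only if the rule is read as every round since joining, which it does not say.

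**3. Who is in the main analysis, read literally.**

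- Enrolled at baseline, tested at every round, any level of lotion use: in.
- Enrolled at baseline, left early, testing stopped: out, whether or not anyone was recruited afterwards.
- Recruited after round 1: out.

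The exclusion of leavers therefore comes from the analysis rule, not from the replacement sentence.

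**4. What differential leaving could do (assumed inputs).** Suppose there is no true effect and loss occurs only in the DEET arm. Let *w* be the share lost and *r* their malaria risk relative to stayers. If stayers have risk *s*, the whole arm has risk *s*(1 − *w* + *wr*), which equals the placebo arm's risk. Analysing stayers only gives

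observed rate ratio = 1 / (1 − *w* + *wr*).

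| *w* | *r* = 0.5 | *r* = 1 | *r* = 2 |
| --- | --- | --- | --- |
| 2% | 1/0.990 = 1.01 | 1.00 | 1/1.02 = 0.98 |
| 5% | 1/0.975 = 1.03 | 1.00 | 1/1.05 = 0.95 |
| 10% | 1/0.950 = 1.05 | 1.00 | 1/1.10 = 0.91 |

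The sign depends on *r*. If leavers have the same risk as stayers there is no bias, and replacing them would change nothing in the expected ratio.

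**5. Scale.** With 8,000 participants, or 4,000 per arm, and the 1.5% incidence behind the 633 households, one arm with no effect expects 4,000 × 0.015 = 60 cases. Ignoring household clustering, the standard error of the log rate ratio is about √(1/60 + 1/60) = 0.18. The largest shift in the table is ln(0.909) = −0.095, about half a standard error. At *w* = 2% and *r* = 2 it is ln(0.980) = −0.020, about a tenth.

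**The case against.** Several objections stand and limit the point.

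- **Further recruitment is only to be considered.** It applies to both arms, and the staff who would do it are blinded to the codes.
- **Leaving is not the only way to stop the lotion.** The protocol expects non-users to remain enrolled. It reports about 27% non-compliance in the first year and defines a separate per-protocol set: "This will include only those participants who slept under a bed net and used the lotion in the evenings at least 90% of the time." Someone who stops using the lotion but keeps testing stays in the initial analysis.
- **Side effects do not vanish.** A reader might infer that people who leave because of a reaction disappear from the safety record. The documents do not support this: "Any contraindications or side effects will be recorded and reported for appropriate action to local District Health departments", and the analysis section assesses adverse events by age group without restricting this to completers.
- **Recruits are not selected for tolerance.** A reader might infer that tolerant late joiners enrich the DEET arm. Recruits have not yet used a trial lotion, nothing ties them to that arm, and on the literal rule those who join after round 1 cannot enter the main analysis at all.
- **Deleting the replacement sentence alone restores nobody to the analysis.** The membership rule must change too.

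It may also be said that handling of withdrawals is commonly left to a statistical analysis plan. That would answer silence. Here, however, the protocol itself fixes both the recruitment rule and the membership rule, and they conflict. How later recruits get an arm is a matter of trial conduct, and follow-up after the lotion is stopped has to be arranged in the field.

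**Conclusion.** The point holds as an inconsistency with a possible bias. The withdrawal, randomisation and analysis sections cannot all be followed as written: recruits have no stated allocation, those added after round 1 are barred from the main analysis, and early leavers whose testing ends are removed from a set labelled intention-to-treat.

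The size is unknown because no withdrawal data are given. Under the assumed losses it is modest, at most about half a standard error on the log scale, and it could go either way. It would therefore be wrong to conclude that efficacy and safety both look better than they should. The documents fix neither the direction for efficacy nor any distortion of the adverse event rate.

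The conclusion assumes that the requirement for a result at every round means what it says, that December is a testing round, and that leavers who withdraw stop being tested. If December is not counted, the maxima fall to 3 of 5 and 5 of 7, and the conclusion is the same.

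**What to change.** 1. **Withdrawal section.** Delete the replacement sentence. State that a participant who wants to stop the lotion is asked whether they will continue the monthly rapid test, the questionnaire and the exit blood spot. Record the main reason for stopping or leaving, and report it by arm.
2. **Analysis section.** Define the main set as all randomised participants, in the arm their household drew, for the time they were observed. The planned Poisson regression with a household random effect can take observed time as an offset, so the model need not change. Observed time keeps results from before a participant left but cannot recover what happened afterwards, which is why step 1 asks for continued testing.
3. **Randomisation section.** Any household enrolled later makes its own draw, is flagged as additional and contributes time from its entry. No individual is added to a household already allocated.

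The cost is protocol wording and one item on the monthly form, since survey visits to these villages already take place. The downside is slight dilution of the estimated effect, because more non-users are counted in the main analysis. The per-protocol analysis still describes regular users.

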### Study Termination

The PI can decide to terminate the trial early if there is concern that the interventions are detrimental to participants’ health.

## STATISTICAL CONSIDERATIONS

### Sample Size Calculation

An initial target of 1,000 households was based on the power calculation below (Table 3). The only reliable clinical data from the study area at the time was 32% prevalence of *P. falciparum* from village surveys during September. The incidence over 9 months sampling was estimated to be 2-6%. Hill *et al.* [23] found 80% reduction in cases in their repellent group and Rowland *et al.* (2004b) found a 44% reduction in *P. falciparum*; therefore a 30-50% reduction was used in the calculations.

Sample sizes were recalculated following the first year’s data collection which found a 0.7% incidence of malaria. A sample size of 633 households per arm would therefore be necessary to detect a 50% intervention effect with 95% significance and 80% power. Non-compliance in the first year was around 27%, so the sample size was adjusted to 804 households per arm.

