## PROTOCOL SUMMARY

Population

Approximately 8,000 rural agricultural workers and children aged from 6 to 60 years, resident in 126 villages in Sekong and Attapeu Provinces in southern Lao PDR.

Sites

One

Study Duration

March 2009 to Feb 2012

Subject Participation Duration

Either 7 months from June to December 2009, or 9 months from April to December 2010

Interventions

1. A single Long-lasting insecticide treated net (PermaNet®2.0, deltamethrin 55mg/m2, mesh 25 holes/cm2) for every 1.5 people in the household

2. 15% DEET lotion or a placebo lotion (both supplied by SCJohnson)

Objectives: The aim of the study is to evaluate the efficacy of 15% DEET insect repellent to reduce malaria incidence in rural populations living in southern Lao PDR.

Study Design: The study will take place in Attapeu and Sekong Provinces in southern Lao PDR and will involve 8000 subjects clustered by household. Participants will be primarily recruited amongst rural agricultural populations who often work and sleep away from the village during the wet season. Either a DEET or placebo lotion will be provided for participants to use every evening. All participants will be supplied with long lasting insecticide treated nets (LLINs). Data collection will take place during June to December of 2009 and April to December of 2010. Malaria cases will be identified through active case detection using RDTs (rapid diagnostic tests) at baseline and at monthly intervals post-intervention. Secondary outcomes are all-cause fevers self reported via monthly questionnaires, and dengue, JE and typhus IgM/IgG from bloodspots collected at baseline and exit.

ClinicalTrials.gov Identifier: NCT00938379

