### Table 4. Revised sample size calculation following first year of data collection (giving a firmer estimate of malaria incidence), calculations are for different scenarios of effect with 95% significance and 80% power

| Assumed Incidence | Intervention Effect | Coefficient of variation (K) | Households Per Arm | Increase 27%  (Loss From Non-Compliance) |
| --- | --- | --- | --- | --- |
| 0.010 | 50% | 0.25 | 948 | 1204 |
| 0.015 | 50% | 0.25 | 633 | 804 |
| 0.020 | 50% | 0.25 | 476 | 605 |
| 0.010 | 40% | 0.25 | 1579 | 2006 |
| 0.015 | 40% | 0.25 | 1054 | 1336 |
| 0.020 | 40% | 0.25 | 792 | 1006 |
| 0.010 | 30% | 0.25 | 2982 | 3787 |
| 0.015 | 30% | 0.25 | 1991 | 2529 |
| 0.020 | 30% | 0.25 | 1495 | 1899 |

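### Table 4 applies one incidence with no stated period to two cohorts of unequal follow-up, and the first-year rate, scaled to the planned follow-up, does not support the stated 80% power

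*Protocol*

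**What the plan says.** The Sample Size Calculation section has two stages. The initial stage (Table 3, target 1,000 households) gives the only period attached to any planning incidence: "The incidence over 9 months sampling was estimated to be 2-6" per cent. The revised stage (Table 4) starts from the first season: "Sample sizes were recalculated following the first year’s data collection which found a 0.7% incidence of malaria". It concludes: "A sample size of 633 households per arm would therefore be necessary to detect a 50% intervention effect with 95% significance and 80% power". The Table 4 row behind this is "0.015 | 50% | 0.25 | 633 | 804", that is, an incidence of 1.5%. The last step is "Non-compliance in the first year was around 27%, so the sample size was adjusted to 804 households per arm". Neither the text nor Table 4 gives a period for the 1.5% or for the 0.7%.

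The households come from two seasons: "when 300 households will be recruited from Attapeu province, and in April 2010, when 1,300 households will be recruited". The Protocol Summary gives participation as "Either 7 months from June to December 2009, or 9 months from April to December 2010". The Follow-up Surveys section says "Monthly surveys will be carried out at monthly intervals after baseline and finishing in December in both years". The Study Schedule puts baseline in June 2009 and April 2010 and the exit survey in December of each year. The Recruitment and Baseline Survey section puts the 2009 baseline in May.

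**The concern.** Malaria is a rare event in this trial, so power depends on the number of cases, and that depends on person-time at risk. A cumulative incidence without a period does not fix the number of cases. The two cohorts are followed for different lengths of time, yet Table 4 credits every household with the same incidence. The 2009 households cannot be set aside, because 300 + 1,300 = 1,600 is what approaches 2 x 804 = 1,608.

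The same missing unit affects the first-year result. The 0.7% was observed over the shorter 2009 season. It has to be converted before it can be compared with a Table 4 row, and the text moves from 0.7% to the 1.5% row with no conversion and no reason given. At stake is whether the 80% power for a 50% effect follows from the data the plan cites.

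**Working it through.** **Inputs.** From the Protocol: 50% effect, k = 0.25, 5% significance (taken as two-sided), 80% power, 633 households per arm before the 27% increase, and 300 and 1,300 households in the two seasons. Persons per household m = 5 is the eligibility minimum, and it agrees with about 8,000 subjects / 1,600 households.

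**Reproducing the plan's figure.** The unmatched cluster formula for rates is

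c = 1 + (1.960 + 0.842)² x [(l0 + l1)/m + k²(l0² + l1²)] / (l0 - l1)²

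With l0 = 0.015 and l1 = 0.0075: c = 1 + 7.849 x (0.0045 + 0.0000176)/0.00005625 = 631.4, against 633 printed. All 19 rows of Tables 3 and 4 reproduce within 3%. The row for 2%, 50%, 0.25 and 80% power is 476 in both tables, so the method did not change between stages. 633 x 1.27 = 803.9, which gives the 804. Inverting the formula at 633 gives power of 80.1%. The formula has no follow-up term: l0 is a cumulative incidence, the same for every household.

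**Average follow-up, by which section is used.**
- Study Schedule (6 and 8 intervals): (300 x 6 + 1,300 x 8)/1,600 = 7.625 months
- May 2009 baseline (7 and 8): (300 x 7 + 1,300 x 8)/1,600 = 7.8125 months
- Protocol Summary (7 and 9): (300 x 7 + 1,300 x 9)/1,600 = 8.625 months

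**Check A: 1.5% read as a 9-month incidence, constant monthly risk.** Expected cases over both arms are 633 x 5 x (l0 + l0/2). At the plan's 1.5% this is 71.

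| Follow-up (months) | Share of 9 months | Control incidence | Expected cases | Power at 633 |
|---|---|---|---|---|
| 6 / 8 | 84.7% | 1.27% | 60 | 73.3% |
| 7 / 8 | 86.8% | 1.30% | 62 | 74.4% |
| 7 / 9 | 95.8% | 1.44% | 68 | 78.4% |

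Other readings of the 1.5%:
- An 8-month figure, with 6 and 8 months of follow-up: 7.625/8 = 95.3% and power 78.2%.
- The average over actual follow-up: no shortfall.
- A figure for the 6-month 2009 season: power rises to about 88%.

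**Check B: the first-year 0.7% carried to the planned follow-up.** Monthly rate = 0.7% / length of the 2009 season, multiplied by the average follow-up above. If 0.7% averages both arms under a 50% effect, the control figure is 0.7%/0.75 before scaling.

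| Follow-up (months) | 0.7% as control rate: incidence, cases, power | 0.7% as both-arm average: control incidence, cases, power |
|---|---|---|
| 6 / 8 | 0.89%, 42, 58.0% | 1.19%, 56, 70.4% |
| 7 / 8 | 0.78%, 37, 52.6% | 1.04%, 49, 64.8% |
| 7 / 9 | 0.86%, 41, 56.7% | 1.15%, 55, 69.1% |

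Taken as it stands, without scaling, 0.7% gives 48% power at 633. Even a conversion from 6 to 9 months for every household gives only 0.7% x 9/6 = 1.05%, or 1.05%/0.75 = 1.4% on the both-arm reading. None of these conversions reaches 1.5%.

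**The case against.** The strongest reply is that the 9-month wording belongs to the initial sizing. The 633 and 804 come from the revised one, which rests on first-year data from a season shorter than 9 months. This stands. A reader might infer that the trial's power is simply 73%, but that needs the 9-month period to be carried over to the 1.5%, and the Protocol does not do so. Check A is therefore conditional.

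A reader might also infer that nobody can be followed for 9 months, because the lotion is issued at baseline. The documents do not support that. The Protocol Summary itself counts April to December 2010 as 9 months, and an early-April baseline with a late-December exit would come close. The Study Schedule supports 8 monthly intervals and no more than that. Likewise, 6 months for 2009 depends on the June baseline, and a May baseline gives 7.

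Three further points have some weight:
- Transmission is seasonal, so a given loss of person-months need not mean the same loss of cases. The Protocol gives no monthly risk from which to do better.
- Households may enrol more than five people. An average of about 5.9 (5/0.847) would offset the largest shortfall in Check A, but the planned 8,000 subjects imply about 5.
- Counting all 804 households as effective gives 83% at 6 and 8 months. Table 4, however, labels the 27% increase as a loss, so 633 is the plan's own effective number.

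None of these replies explains the step from 0.7% to 1.5%.

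**Conclusion.** The point holds in two parts of different size.

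First, Table 4 uses an incidence with no period for cohorts whose follow-up differs, and the sections giving that follow-up disagree. On the only period the Protocol states, and with constant monthly risk, person-time is about 4-15% short and power at 633 per arm is about 73-78%. On other readings of the 1.5% there is no shortfall from this source, or even a gain.

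Second, and more firmly, the first-year rate does not lead to the row used. Scaled to the planned follow-up it is about 0.8-0.9%, with about 53-58% power, or about 65-70% if it is a both-arm average under a 50% effect. The stated 80% is therefore not supported by the first-year figure from which the text says it follows. These results assume m = 5, k = 0.25, constant monthly risk, and the first-year rate applying to the 2010 villages. A higher rate in 2010, when Sekong is added, could justify more than 0.8-0.9%, but the plan makes no such argument.

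It would be wrong to infer from this that the trial must be enlarged. What fails is the stated justification of the power.

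**What to change.** - Reconcile the Protocol Summary, Study Schedule and Recruitment and Baseline Survey sections on the 2009 baseline month and on the length of follow-up in each season.
- State the planning incidence per person-month at risk after lotion issue. Convert the first-year 0.7% to that unit, and say whether it is a control-arm or a both-arm figure.
- Justify the 1.5%, for example by the difference between the 2009 and 2010 areas, or replace it.
- Recompute Table 4 from the planned person-months of each cohort, including rows at the converted first-year rate, since the lowest row now is 1.0%.
- Restate the power and expected number of cases of the 1,600-household trial as a range under stated assumptions. A single replacement figure such as 73% should not be printed, because it would still rest on the unexplained 1.5%.

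The cost is a recalculation and rewording of the Sample Size Calculation section and Table 4, and a less favourable stated power. No change in enrolment is asked for.

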## PARTICIPANT AND HOUSEHOLD ELIGIBILITY

Participants will be on primarily recruited amongst rural agricultural workers that often work and sleep overnight away from the village during the wet season. Households must enrol at least five eligible participants to enter the trial. Participants must be aged 6-60 years to take part in the trial.

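### The revised sample size of 633 (804) households per arm is said to follow from the 0.7% first-year incidence, but in Table 4 it belongs to an assumed incidence of 1.5%, and no step connects the two

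*Protocol*

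**What the plan says.** The Sample Size Calculation section of the protocol bases the revision on the first year's data collection, "which found a 0.7% incidence of malaria. A sample size of 633 households per arm would therefore be necessary" for a 50% effect at 95% significance and 80% power. The section then raises the figure to 804 per arm because first-year non-compliance was around 27%.

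Table 4 is captioned as the revision made once the first year had given a firmer estimate of incidence. The figures 633 and 804 appear there on one row only, with columns for assumed incidence, effect, k, households per arm and inflated households: "0.015 | 50% | 0.25 | 633 | 804". The lowest incidence tabulated at the same effect is 1.0%: "0.010 | 50% | 0.25 | 948 | 1204". No row is at or near 0.7%.

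The Recruitment and Baseline Survey section sets enrolment for May 2009 and April 2010: "when 300 households will be recruited from Attapeu province, and in April 2010, when 1,300 households will be recruited". That is 1,600 households, or about 800 per arm, so the 1.5% row is the one the trial adopted.

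**The concern.** The text presents 633 as the consequence of an observed 0.7%, while the table derives it from an incidence more than twice as high. No sentence explains the move from one to the other.

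This is the only power justification for the malaria outcome, and it sets the enrolment. With 4,000 people per arm (800 households of 5), a control risk of 0.7% and a 50% effect imply about 28 control and 14 DEET cases. At 1.5% the figures are 60 and 30. Someone relying on the stated 80% power needs to know which of these the trial was designed for.

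**Working it through.** **Inputs.** Effect 50%, 95% significance (read as two-sided 5%), 80% power and k = 0.25 come from the Sample Size Calculation section and Table 4. The number of participants per household, m = 5, is not stated as an input. It is inferred from the eligibility rule ("Households must enrol at least five eligible participants to enter the trial"), from about 8,000 subjects over 1,600 households, and from the fact that m = 4 and m = 6 do not reproduce Table 4.

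**Formula.** For an unmatched cluster trial with rates, households per arm are

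c = 1 + (z₀.₉₇₅ + z₀.₈₀)² × [(r0 + r1)/m + k²(r0² + r1²)] / (r0 − r1)², with (1.960 + 0.842)² = 7.849.

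**Reproducing the plan's figures.**

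- r0 = 0.015, r1 = 0.0075: (r0 + r1)/5 = 0.0045; k²(r0² + r1²) = 0.0000176; (r0 − r1)² = 0.00005625. So c = 1 + 7.849 × 0.0045176/0.00005625 = 631.4, against 633 stated.
- r0 = 0.010: c = 945.3, against 948 stated.
- All nine rows of Table 4 and all ten rows of Table 3 are reproduced within about 0.4%.
- 633 × 1.27 = 803.9, which matches 804.

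The table's arithmetic is sound. The fault lies in the link between text and row.

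**Same method at 0.7%.** r0 = 0.007, r1 = 0.0035: (r0 + r1)/5 = 0.0021; k²(r0² + r1²) = 0.0000038; (r0 − r1)² = 0.00001225. So c = 1 + 7.849 × 0.0021038/0.00001225 = 1,349, and 1,349 × 1.27 = 1,713. This is about 2.1 times 633. The proportions version of the formula gives 1,341, and k = 0 gives 1,347. About 11 participants per household would be needed before 633 sufficed.

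**Power for a 50% effect.** Power = Φ(√{(c − 1)(r0 − r1)² / [(r0 + r1)/m + k²(r0² + r1²)]} − 1.96). The columns assume full compliance.

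| Control incidence | Households per arm for 80% | Power, 633 per arm | Power, 800 per arm |
| --- | --- | --- | --- |
| 0.70% | 1,349 | 48% | 58% |
| 0.93% | 1,013 | 60% | 70% |
| 1.24% | 760 | 72% | 82% |
| 1.50% | 631 | 80% | 88% |

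**Where the middle rows come from.** The Study Schedule gives 6 post-baseline rounds in 2009 (July to December) and 8 in 2010 (May to December). Scaling gives 0.7% × 8/6 = 0.93%. Alternatively, if 0.7% pools both arms under a 50% effect, then 0.7% = 0.75 × r0, so r0 = 0.93%. Applying both steps gives 0.93%/0.75 = 1.24%.

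**The case against.** The strongest reply is that 1.5% is an assumed incidence for the trial as a whole and that the protocol contains material to support it. The first year recruited in Attapeu only, and the second adds Sekong. The Background gives 1998 prevalence of 101 per 1,000 in Attapeu and 163 per 1,000 in Sekong, a ratio of 1.61. If second-year recruitment were split 50:50 (an assumption, since the split is not given), the average multiplier would be (1 + 1.61)/2 = 1.31. Applied to 1.24%, this gives about 1.63%, which needs about 583 households per arm, fewer than 633. So a forecast near 1.5% is conceivable, and a reader who inferred that nothing in the protocol could lead to it would be wrong.

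The time unit of 0.7% is also unstated. Read as a monthly rate, it becomes about 5.6% over 8 rounds, where about 172 households per arm suffice. A reader might therefore infer from the mismatch that the trial is certainly underpowered. The documents do not support that: the shortfall depends on the unit of the 0.7% and on whether it carries over to 2010.

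Both replies stand against the size of the shortfall. Neither repairs the statement itself. The protocol offers none of this reasoning and says that 633 follows from 0.7%. On the monthly reading 633 does not follow either, because it would then be far too many.

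A reader might also take the 27% off the 800 households and quote 45% power at 0.7% with 584 per arm. That figure describes losing 27% of households. It is not the power of the intention-to-treat analysis, in which non-compliers who meet its data requirement stay in and dilute the effect.

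Finally, the planned 1,600 households against 2 × 804 = 1,608 is rounding and not a defect.

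**Conclusion.** The statement is wrong as written. The text and Table 4 disagree on the incidence behind 633 and 804, and this is certain from the two passages without any calculation.

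The size of the consequence is conditional. If 0.7% is a per-season risk on Table 4's scale and applies throughout the trial, with m = 5, k = 0.25 and a 50% effect, the requirement is about 1,349 per arm (1,713 inflated). Power is then about 58% with 800 per arm before any non-compliance, against the claimed 80%. At 0.93% it is 70%. At 1.24% it is 82%, so the claimed power would be met at full compliance, with no margin left for the 27% non-compliance the plan allows for. The protocol does not give enough to say which case applies.

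**What to change.** In the Sample Size Calculation section, state the time unit and denominator of the 0.7%: per season, per month or per person-year, and whether it pools the arms. Then do one of the following:

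- Add a 0.007 row to Table 4 (about 1,349 per arm, 1,713 after the plan's inflation, if the figure is a per-season risk) and restate the power of about 800 households per arm at that incidence.
- State 1.5% as the design incidence, justify the step from 0.7% (season length, pooled arms, the addition of Sekong), and report power across 0.7% to 1.5%.

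The cost is a few sentences and one table row or a short power table. No extra enrolment is requested. Under the first option the stated power becomes less favourable.
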